### Data analysis

Data analysis for this study is tailored to each specific study objective. All final analyses will be conducted by an assigned study statistician or through common statistical packages disseminated to each study site. Descriptive data of the study cohort will be presented with medians and interquartile ranges for continuous variables and number and percentages for categorical variables. This will be presented in an overall, pooled format, as well as stratified by study sites and study time-period.

The main exposure of interest, SARS-CoV-2 variants, will be studied using both the currently described genotypes of main interest and a subset of whole genome sequencing data. Depending on local and temporal variations in circulating variants and the percentage of hospitalised patients with variant classification performed, the variant might be extrapolated based on the current variant distribution.

The primary outcome, in-hospital mortality, will be studied using Cox proportional hazards models and Fine and Gray models, with the underlying baseline hazard function based on the date of admission or the date of the first positive test if tested positive later during hospitalisation. Patients with community-onset and hospital-onset COVID-19 will be analysed both pooled and separately. Competing risks analyses will be used to examine ICU admission, length of hospitalisation, and length of ICU stay, with in-hospital death as a competing event.

Covariate adjustment will be used to control for potential confounding variables, including age, sex, ethnicity, co-morbidities in accordance with risk factors for severe COVID-19 according to the Centre for Disease Control and Prevention (CDC), SARS-CoV-2 vaccination status, and geographical region. Both complete case analyses and analyses based on multiple imputation by chained equations imputed or inverse probability weighted datasets will be performed to account for missing data.

Given the evolving nature of COVID-19, covariates as well as other variables and definitions may change over the course of the pandemic. The effect of various interventions performed during hospitalisation on the study objectives will be evaluated using causal inference methods, including inverse propensity weighting and doubly robust methods, to account for potential treatment biases and violations of positivity assumptions.

Finally, machine learning (ML) methods will be used to analyse data, including unsupervised ML methods for heterogeneous multi-view data and supervised ML methods that correct for phylogenetic relationships and other potential biases. These state-of-the-art methods will provide a comprehensive and nuanced understanding of the data and its implications for the study objectives.

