## Abstract

**Background:**

Severe acute respiratory syndrome coronavirus 2 (SARS CoV-2), the virus responsible for coronavirus disease 2019 (COVID-19), can lead to hospitalisation, particularly in elderly, immunocompromised, and non-vaccinated or partially vaccinated individuals. Although vaccination provides protection, the duration of this protection wanes over time. Additional doses can restore immunity, but the influence of viral variants, specific sequences, and vaccine-induced immune responses on disease severity remains unclear. Moreover, the efficacy of therapeutic interventions during hospitalisation requires further investigation. The study aims to analyse the clinical course of COVID-19 in hospitalised patients, taking into account SARS-CoV-2 variants, viral sequences, and the impact of different vaccines. The primary outcome is all-cause in-hospital mortality, while secondary outcomes include admission to intensive care unit and length of stay, duration of hospitalisation, and the level of respiratory support required.

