### Study population

The study population includes adult patients (≥ 18 years) who are hospitalised or who have died in the emergency department and have tested positive for SARS-CoV-2 by polymerase chain reaction (PCR) or by an antigen test within 14 days prior to admission or during hospitalisation. The study aims to include both first and recurrent episodes of COVID-19. All study subjects are required to sign informed consent when required by ethical approval. Patients who do not meet these inclusion criteria will be excluded from the study.

The anticipated sample size for the study is 35,000, which is expected to increase depending on the course of the COVID-19 pandemic. Due to the recruitment strategy of the study, the exact sample size cannot be predetermined as it is dependent on the number of patients admitted to participating centres. This approach will provide a diverse cohort of patients from various geographical regions, with a range of demographic and clinical characteristics, thus establishing a robust foundation for the study's research objectives (Fig. 1).

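### For ICU admission the plan names only in-hospital death as a competing event; discharge alive without ICU is left out, and censoring it would overstate ICU risk

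*Protocol article*

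**What the plan says.** All statements are in the protocol article.

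- **Secondary outcomes (Data analysis).** One competing event is given for three outcomes together: "ICU admission, length of hospitalisation, and length of ICU stay, with in-hospital death as a competing event". Discharge alive is not mentioned anywhere in the article, either as a competing event or as a reason for censoring.
- **Primary outcome (Abstract and Data analysis).** "The primary outcome is all-cause in-hospital mortality". "The primary outcome, in-hospital mortality, will be studied using Cox proportional hazards models and Fine and Gray models". The competing event of the Fine and Gray model is not named.
- **Time origin (Data analysis, stated for the primary outcome).** "the underlying baseline hazard function based on the date of admission or the date of the first positive test if tested positive later during hospitalisation".
- **Exposure (Data analysis).** "The main exposure of interest, SARS-CoV-2 variants". The Aims and objectives section also asks about vaccines and vaccination schedules, and lists both ICU admission and overall length of hospitalisation among the outcomes.

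**The concern.** The three outcomes in the sentence do not have the same structure. For length of hospitalisation and length of ICU stay, the event is leaving, and death is what prevents it. For ICU admission, the event can be prevented in two ways: by death without ICU, and by discharge alive without ICU. Only the first is named.

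In a competing-risks model, an exit that is neither the event nor a named competing event is ordinarily censored. Censoring at discharge treats those who went home as having the same future ICU risk as those still in hospital. Their in-hospital risk is zero, so the estimated cumulative incidence becomes too high.

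This bears on the study's own questions. ICU admission is one of the measures of variant and vaccine impact, and whether length of hospitalisation differs by variant or vaccine is itself under study. If discharge speed does differ, the size of the distortion differs between the groups compared. The large planned sample does not reduce such a bias.

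**Working it through.** **Nothing to reproduce.** The article gives no event rate, effect size or power. Its one size figure is a recruitment forecast: "The anticipated sample size for the study is 35,000, which is expected to increase depending on the course of the COVID-19 pandemic". All rates below are therefore assumptions, shown over a range.

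**Formula.** Take constant daily hazards: *a* for ICU admission, *d* for death without ICU, *c* for discharge alive without ICU.

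- Discharge as a competing event: risk by day *t* = a/(a+d+c) × (1 − exp(−(a+d+c)t)).
- Discharge censored, death still competing: a/(a+d) × (1 − exp(−(a+d)t)).

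**Base case (assumed).** First exit is ICU in 15%, death without ICU in 8% and discharge without ICU in 77%, with a mean time to first exit of 10 days. So a = 0.015, d = 0.008, c = 0.077.

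- 28 days, discharge competing: 0.015/0.100 × (1 − exp(−2.8)) = 14.1%.
- 28 days, discharge censored: 0.015/0.023 × (1 − exp(−0.644)) = 31.0%, which is 2.2 times as high.
- 60 days: 15.0% against 48.8%, or 3.3 times.

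**Range of assumptions.**

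| ICU / death without ICU | Mean days to first exit | 28 days: competing | 28 days: censored | Ratio at 28 days | Ratio at 60 days |
|---|---|---|---|---|---|
| 10% / 5% | 7 | 9.8% | 30.1% | 3.06 | 4.82 |
| 10% / 5% | 10 | 9.4% | 22.9% | 2.43 | 3.97 |
| 15% / 8% | 7 | 14.7% | 39.2% | 2.66 | 3.74 |
| 15% / 8% | 10 | 14.1% | 31.0% | 2.20 | 3.26 |
| 25% / 10% | 7 | 24.5% | 53.8% | 2.19 | 2.72 |
| 25% / 10% | 10 | 23.5% | 44.6% | 1.90 | 2.51 |

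A separate set of assumed hazards (ICU 2%, death 0.5%, discharge 9% per day) falls inside this range: 0.02/0.115 × (1 − exp(−3.22)) = 16.7% against 0.02/0.025 × (1 − exp(−0.7)) = 40.3%, a ratio of 2.4.

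**Contrast between two variants at 28 days.** The reference group is the base case (14.1% competing, 31.0% censored). The death hazard is unchanged except in the fourth row.

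| Second variant | Risk, discharge competing | Risk ratio | Risk, discharge censored | Risk ratio | Effect of censoring |
|---|---|---|---|---|---|
| Same ICU hazard, discharge ×1.5 | 10.6% | 0.75 | 31.0% | 1.00 | difference hidden |
| ICU hazard ×0.6, same discharge | 8.9% | 0.63 | 20.1% | 0.65 | kept |
| ICU hazard ×0.6, discharge ×1.5 | 6.6% | 0.47 | 20.1% | 0.65 | attenuated |
| All hazards ×0.7 | 12.9% | 0.91 | 23.7% | 0.76 | exaggerated |
| ICU and discharge hazards ×1.5 | 15.2% | 1.08 | 42.4% | 1.37 | exaggerated |

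The absolute risk is overstated in every scenario. The relative comparison has no fixed direction of error.

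**The case against.** The strongest reply is that the article never says discharged patients are censored. It calls death a competing event, not the only one, and the sentence may simply list the competitor common to three outcomes, two of which it describes correctly. If discharged patients were kept event-free to a fixed horizon, the cumulative incidence of in-hospital ICU admission would be right with death as the only named competitor. The full protocol or analysis plan may settle this. It is also true that a hazard ratio censored at discharge is valid as a cause-specific rate ratio, that the article promises no model-based absolute ICU risks, and that its descriptive counts and percentages are unaffected.

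Most of that stands, and it limits the point. It does not remove it. The article chose to state the competing event and stated it incompletely for one outcome; a programmer who follows the sentence literally will censor discharge.

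Two stronger readings are tempting, and the document supports neither.

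- *That the primary outcome has the same fault.* A Fine and Gray model is planned for in-hospital mortality. Because the outcome is death from any cause in hospital, the only possible competing event is leaving hospital alive, so the model implies it. The article proposes no Kaplan-Meier mortality risk censored at discharge. What is left is an unnamed event and an unlabelled Cox hazard ratio.
- *That the rule hides differences between variants.* That is one possible result. As the second table shows, a contrast may also be kept, attenuated or exaggerated.

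Nor does the point reach the ventilation outcomes, for which the Data analysis section names no time-to-event method.

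**Conclusion.** The sentence is incomplete for ICU admission, a secondary outcome, and correct for length of hospitalisation and length of ICU stay. Applied as written with discharge censored, it would overstate the cumulative incidence of ICU admission about 2 to 3 times at 28 days (1.9 to 3.1) and 2.5 to 4.8 times at 60 days. It could also distort risk contrasts between variant or vaccine groups in either direction when discharge speed differs.

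This rests on two assumptions: that discharge is censored, which is the ordinary consequence of the wording but is not stated; and constant hazards at the assumed rates, none of which come from the document. The size changes with the rates, but the overstatement appears in every scenario tried. For the primary outcome there is no error, only something to make explicit.

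**What to change.** In the Data analysis section, separate ICU admission from the two length-of-stay outcomes:

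1. For ICU admission, name death without ICU and discharge alive without ICU as competing events. For cumulative incidence, keeping discharged patients event-free to a fixed horizon is equivalent.
2. State that any hazard ratio for ICU admission censored at discharge is cause-specific and is not to be read as a ratio of risks.
3. Leave death as the competing event for length of hospitalisation and length of ICU stay.
4. As a clarification only, name discharge alive as the competing event in the Fine and Gray model for in-hospital mortality, and label the Cox hazard ratio cause-specific.

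The cost is a phrase or two before analysis. Length of hospitalisation is already an outcome, so discharge timing is needed in any case. Because the section allows analyses to be run at individual sites with shared statistical packages, fixing the wording centrally also prevents sites from handling discharge differently.

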## Discussion

The EuCARE project is a multifaceted initiative that aims to provide an advanced response to the ongoing COVID-19 epidemics. Among the various cohorts within the EuCARE project, the EuCARE-HOSPITALISED study stands out for its focus on assessing the relationship between different circulating variants and the risk of in-hospital mortality. It defines a wide range of variables, including epidemiological and clinical factors, as well as advanced laboratory features, to analyse the progression, management, and outcomes of COVID-19 disease. One of the key strengths of the EuCARE-HOSPITALISED study is its large sample size, which makes it one of the largest cohorts studied to date. This provides increased statistical power to detect even subtle relationships between different circulating variants and in-hospital mortality. Additionally, the study's wide range of variables allows for a comprehensive analysis of the progression, management, and outcomes of COVID-19 disease, incorporating epidemiological and clinical factors, as well as advanced laboratory features. Furthermore, the collection of biologic samples from hospitalised patients in the EuCARE-HOSPITALISED study offers opportunities for future research on important aspects that have not yet been investigated. This is particularly relevant as COVID-19 is a relatively new disease, and much is still unknown about its pathophysiology, clinical presentation, and long-term outcomes. Another notable aspect of the EuCARE-HOSPITALISED study is its collaboration with machine-learning experts. By leveraging the power of artificial intelligence (AI) to integrate both patient and viral data, researchers can develop advanced predictive models that may help identify patients at higher risk of in-hospital mortality and guide clinical decision-making. The long duration of the EuCARE-HOSPITALISED study is also noteworthy. Covering different phases and waves of COVID-19, along with differences in viral characteristics, clinical management, and vaccination status, it provides a dynamic perspective on the disease and epidemics. This is crucial considering the rapidly evolving nature of COVID-19, where factors influencing disease progression and outcomes may change over time. Moreover, it's important to highlight that the EuCARE-HOSPITALISED study benefits from the insights provided by a distinguished external scientific and stakeholder advisory board, as well as an ethics advisory board. Finally, The EuCARE-HOSPITALISED study aims to investigate the clinical outcome and differences in mortality among COVID-19 patients based on their response to antivirals and the booster vaccination dose received.

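### The confounders named for the variant–mortality models do not include calendar period, although variant and clinical management changed together across waves

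*Protocol article*

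**What the plan says.** All but the last two items come from the Data analysis section of the protocol article.

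- Exposure: "The main exposure of interest, SARS-CoV-2 variants, will be studied using both the currently described genotypes of main interest", together with a subset of whole-genome data. Where typing is incomplete, "the variant might be extrapolated based on the current variant distribution".
- Primary outcome: in-hospital mortality by Cox and Fine-Gray models, "with the underlying baseline hazard function based on the date of admission or the date of the first positive test" if the test came later in the stay.
- Adjustment: "Covariate adjustment will be used to control for potential confounding variables, including age, sex, ethnicity, co-morbidities" chosen by published risk factors for severe disease, and then "SARS-CoV-2 vaccination status, and geographical region". The section adds that covariates and definitions may change as the pandemic evolves.
- Site and period appear in one place, for the descriptive data: "This will be presented in an overall, pooled format, as well as stratified by study sites and study time-period".
- The Discussion presents the long duration as a strength: "Covering different phases and waves of COVID-19, along with differences in viral characteristics, clinical management, and vaccination status".
- The limitations paragraph of the Discussion concedes unmeasured confounding in general, and variant characterisation that differed by period and site. It attaches no adjustment to either.

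**The concern.** Variants replaced one another over calendar time. On the document's own account, clinical management moved with them. Calendar period is therefore linked both to the main exposure and to causes of death other than the virus. It is also measured, because the admission and test dates already define the start of follow-up.

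Of the two non-viral factors that the Discussion says changed across waves, vaccination is in the named set and clinical management is not. Extrapolation sharpens the problem: where variant is assigned from the distribution at that time and place, the exposure is itself a function of date and location.

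At stake is the reading of the study's main estimate. A difference in mortality between variants could be reported as a difference in severity when part of it reflects care or admission thresholds in that period. A large cohort does not protect against this; it narrows the interval around the wrong value.

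**Working it through.** The article derives no figure that could be reproduced here. The 35,000 patients are an expected intake, and no mortality rate, effect size or power is given. The check is therefore a reading of the text plus an illustration on assumed inputs.

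**Reading.** Named covariates: age, sex, ethnicity, co-morbidities, vaccination status, geographical region. Calendar period is not among them, nor is it named as a stratum. The time origin is admission or first positive test, so the baseline hazard describes time within the stay and does not absorb calendar time.

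**Size of the distortion (all inputs assumed).** Take two periods of equal size and a true variant hazard ratio of 1. Let g be the late-versus-early mortality ratio from non-viral changes not captured by the covariates. Let s be the new variant's share in the early period and 1 − s its share in the late one. Ignoring period,

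apparent ratio = [s + (1 − s)g] / [(1 − s) + s·g].

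For g = 0.8:

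- s = 0.30: (0.30 + 0.56)/(0.70 + 0.24) = 0.86/0.94 = 0.915
- s = 0.10: (0.10 + 0.72)/(0.90 + 0.08) = 0.82/0.98 = 0.837
- s = 0: 0.80, which is the assumed input returned unchanged

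| g | s = 0.30 | s = 0.10 | s = 0 |
|---|---|---|---|
| 0.9 | 0.96 | 0.92 | 0.90 |
| 0.8 | 0.92 | 0.84 | 0.80 |
| 0.7 | 0.87 | 0.75 | 0.70 |

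**Would it look significant?** With equal groups, SE(log HR) = 2/√D for D deaths, and the chance of two-sided p < 0.05 is about Φ(|ln HR|/SE − 1.96). For an apparent ratio of 0.837, |ln HR| = 0.178. Mortality of 1%, 5% and 10% of 35,000 is assumed.

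| Deaths | SE | \|ln HR\|/SE | Chance of p < 0.05 |
|---|---|---|---|
| 350 | 0.107 | 1.66 | 38% |
| 1,750 | 0.048 | 3.72 | 96% |
| 3,500 | 0.034 | 5.26 | about 100% |

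These are upper-end figures. They put the whole cohort into one balanced two-variant contrast, whereas variant data are collected only when available and the study spans several waves.

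**Price of adjusting.** In this set-up the correlation of variant with period is r = 1 − 2s, and adding period inflates the variance of the variant effect by 1/(1 − r²).

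- s = 0.30: r = 0.4, 1/0.84 = 1.19
- s = 0.10: r = 0.8, 1/0.36 = 2.78, so 35,000 patients carry the information of 35,000 × 0.36 = 12,600
- s = 0.01: r = 0.98, 1/0.0396 = 25
- s = 0: variant and period cannot be separated

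**The case against.** The strongest reply is that the list is open: it is introduced as examples, the covariates may change, and this is a condensed article whose full analysis plan is not shown. Nothing in it excludes calendar period. That stands, and it limits the claim. A reader might infer that the main estimate *is* biased, or that variant would absorb *every* change over time. The document supports neither. Age, co-morbidities and vaccination status are named, so part of the shift in case mix between waves is handled. What remains is change in care and admission thresholds. Still, the article does state an adjustment set, and that set names ethnicity and region while passing over a measured factor closely tied to the exposure. Permission to change covariates later commits to nothing.

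A reader might also infer that differences between centres are uncontrolled. That depends on what region means, which the article does not define. The Aims and objectives section gives twelve hospitals or clinics in eleven countries on four continents. If region means country, it is almost the same as centre; if continent, much between-centre difference could remain. This supports asking for a definition and no more.

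The separate causal-inference analyses concern the effects of in-hospital interventions and do not adjust the variant model. The general caveat about unmeasured confounding does not cover a factor that is measured.

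Finally, adjustment costs precision and fails where variants did not overlap. That is true. In that case, however, the data cannot separate variant from period, and leaving period out of the model does not change this.

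**Conclusion.** The point holds for calendar period as the adjustment set is stated. The named confounders do not control for it, and on the document's own account it is linked to both variant and clinical management. Because this touches the main exposure and the primary outcome, it should be settled before the variant models are fitted.

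The size cannot be established from the document. If non-viral causes not captured by the covariates lowered mortality by 20%, a null variant would appear as a hazard ratio of about 0.92 (30% overlap), 0.84 (10%) or 0.80 (none). Across falls of 10% to 30%, the range is 0.96 to 0.87 at 30% overlap and 0.92 to 0.75 at 10%. The value 0.80 is the no-overlap extreme and should not be quoted as the expected bias. The fall in mortality, the overlap and the death counts are all assumptions.

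**What to change.** 1. Add calendar time of admission or positive test, as a spline or period strata, to the Cox and Fine-Gray variant models.
2. Define geographical region as country or centre, or stratify the baseline hazard by centre.
3. Exclude patients whose variant was extrapolated from calendar time from the period-adjusted variant contrast, since their exposure carries little or no information beyond date and place.
4. Report a within-period comparison for times when the variants co-circulated, and state that contrasts between variants with no overlap in time cannot be separated from period.

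Whether the co-circulation comparison should be the primary contrast is a trade-off for the study team; adding calendar time to the model is the essential step.

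No new data are needed, because the dates are already collected. The cost is statistical: wider confidence intervals (on the assumed inputs, variance about 1.2 times at 30% overlap and 2.8 times at 10%), fewer patients in the period-adjusted contrast, and some variant pairs that cannot be estimated.

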## Background

Since the onset of the coronavirus disease 2019 (COVID-19) pandemic, novel variants of severe acute respiratory syndrome coronavirus 2 (SARS-CoV-2) have emerged. The World Health Organization (WHO) categorises these variants based on level of concern, including variant of interest (VOI), variant of concern (VOC), and variants under monitoring (VUM) [1]. The VOC known as Omicron (B.1.1.529) was designated by the WHO on November 26, 2021 [2]. In contrast, the European Centre for Disease Prevention and Control (ECDC) removed BA.2, BA.4, and BA.5 variants from their list of concern due to their limited circulation [3].

To better understand the impact of these variants, detailed information is needed regarding their severity, mortality rates, disease progression, and the effectiveness of currently available vaccines and therapeutic interventions. Notably, previous reports have suggested increased disease severity for the B1.1.1.7 (alpha) variant compared to other co-existing and previous variants [4–6].

Recent studies have indicated that the Omicron variant poses lower risks of hospital attendance, admission, and death when compared to the Delta variant [7–9]. While the likelihood of severe disease from Omicron is lower compared to previous variants, the sheer volume of cases associated with it has led to a cumulative increase in hospitalisations related to COVID-19, surpassing those caused by other variants [10]. The diminished likelihood of severe disease associated with Omicron could be a result of partial immunity acquired through previous infection or vaccination. Additionally, findings from animal studies, wherein Omicron infections exhibited lower viral levels in infected tissues, lend further support to the notion that Omicron may inherently induce a less severe infection when compared to alternative variants [11].

The influence of different SARS-CoV-2 variants on COVID-19-specific therapies, such as antivirals and immunomodulators, remains to be thoroughly elucidated. Evidence suggests that widely used monoclonal antibody cocktails exhibit reduced efficacy against the Omicron variant, while antivirals continue to be effective [12–17].

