### Aims and objectives

The aims of this study are to analyse the clinical course of COVID-19 in hospitalised patients in relation to SARS-CoV-2 viral characteristics and vaccines used and to provide recommendations for optimised clinical management and treatment, taking into consideration the viral characteristics and vaccines employed. Data and biological material from COVID-19 inpatients in a diverse setting of twelve hospitals/clinics across eleven countries and four continents are being collected and will be analysed.

The specific objectives of this study are:To describe the patterns of clinical symptoms, therapeutic interventions, and clinical outcomes in patients hospitalised for SARS CoV-2 infection.To assess the impact of viral variants/sequences on clinical outcomes measured by all-cause in-hospital mortality, non-invasive mechanical ventilation/high-flow nasal oxygen, mechanical ventilation, admission to the intensive care unit (ICU), length of ICU stay, and overall length of hospitalisation.To assess the impact of different vaccines and vaccination schedules on clinical outcomes (vaccine effectiveness for progression/pathogenesis) measured by all-cause in-hospital mortality, non-invasive mechanical ventilation/high-flow nasal oxygen, mechanical ventilation, admission to the ICU, length of ICU stay, and overall length of hospitalisation, with the goal of enhancing our comprehension of vaccine hesitancy.To assess the impact of viral variants/sequences, different vaccines and vaccination schedule on response to treatment interventions and the associated clinical outcomes.To provide biological material to Work Package 2 (WP2) in EuCARE for further studies on viral characteristics and associated immune responses.To provide data to Work Package 5 (WP5) in EuCARE for further studies using machine-learning approaches.

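### The protocol says inverse propensity weighting and doubly robust methods deal with positivity violations, but both methods assume positivity

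*Protocol article*

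**What the plan says.** The Data analysis section of the protocol article gives one sentence to the effects of treatment given in hospital: "The effect of various interventions performed during hospitalisation on the study objectives will be evaluated using causal inference methods". It names two methods and their purpose: "inverse propensity weighting and doubly robust methods, to account for potential treatment biases and violations of positivity assumptions". The text shown ties no other technique to positivity, and the limitations in the Discussion do not mention it.

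Three other statements bear on whether positivity could fail:

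- Data come from "twelve hospitals/clinics across eleven countries and four continents" (Aims and objectives).
- The Discussion describes the study as "Covering different phases and waves of COVID-19, along with differences in viral characteristics, clinical management, and vaccination status".
- The Background reports that "widely used monoclonal antibody cocktails exhibit reduced efficacy against the Omicron variant, while antivirals continue to be effective", so the authors themselves expect some treatment effects to depend on the variant, and hence on the period.

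Response to treatment is one of the specific objectives, and the aims include recommendations on treatment.

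**The concern.** Positivity means that, at every combination of the covariates adjusted for, the probability of treatment lies strictly between 0 and 1. Inverse weighting divides by that probability. A group with probability 0 has no treated patients to weight up and disappears from the treated arm, while staying in the untreated arm. Probabilities near 0 or 1 give extreme weights. A standard doubly robust estimator needs positivity for its robustness property. In a group with no treated patients it has only the outcome model, fitted on other patients, to supply the missing risk.

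The sentence therefore presents a condition of the methods as something they repair. An analyst who takes it at its word could skip the overlap check and the restriction that is needed. Where availability changed between waves, a change in mortality over time could then appear as a treatment effect.

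**Working it through.** The protocol gives no figure on this point, so there is none to reproduce. All risks, propensities and shares below are assumptions chosen to show the mechanism.

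**1. Illustration with no treatment effect.** A share s = 0.40 of patients is in a period without the drug (propensity e = 0, mortality m1 = 0.20). The other 0.60 are in a period with e = 0.5 and mortality m2 = 0.10, treated or not. The true risk ratio is 1.0.

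Normalised whole-cohort inverse weighting with the correct propensities:

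- Treated: only the second period contributes, so the mean is 0.10.
- Untreated: weights 1/(1 − e) are 1 and 2. The weight total is 0.4 × 1 + 0.6 × 0.5 × 2 = 1.0. The mean is 0.4 × 0.20 + 0.6 × 0.5 × 2 × 0.10 = 0.08 + 0.06 = 0.14.
- Risk ratio: 0.10 / 0.14 = 0.71.

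Alternatives on the same inputs:

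- Restriction to the second period: 0.10 against 0.10, risk ratio 1.0.
- Weights for the effect in the treated, e/(1 − e) for untreated patients: 0 in the first period and 1 in the second, so 0.10 against 0.10, risk ratio 1.0.
- Doubly robust, with period and a common treatment effect in the outcome model: 0.4 × 0.20 + 0.6 × 0.10 = 0.14 in both arms, risk ratio 1.0. This is right only because the common effect is true here.

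**2. Range.** In general the false ratio is m2 / (s × m1 + (1 − s) × m2).

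| s | m1 | m2 | Denominator | False risk ratio |
|---|---|---|---|---|
| 0.40 | 0.20 | 0.10 | 0.08 + 0.06 = 0.14 | 0.71 |
| 0.20 | 0.20 | 0.10 | 0.04 + 0.08 = 0.12 | 0.83 |
| 0.40 | 0.15 | 0.10 | 0.06 + 0.06 = 0.12 | 0.83 |
| 0.40 | 0.10 | 0.10 | 0.04 + 0.06 = 0.10 | 1.00 |
| 0.40 | 0.05 | 0.10 | 0.02 + 0.06 = 0.08 | 1.25 |

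The bias vanishes when the periods have equal mortality and changes direction when the drug-free period has the lower mortality.

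**3. Simulation with a real effect.** Size 35,000 (Study population: "The anticipated sample size for the study is 35,000"), 60 replicates. A binary confounder X with prevalence 0.5 sets the propensity at 0.3 or 0.6. A group V (20% or 40% of patients) is never treated. Untreated risk is 0.10 + 0.10X + 0.08V. The true risk difference is −0.04 outside V, and −0.04, 0 or +0.04 inside V. The doubly robust estimator uses an outcome model with a common effect.

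| Share in V | True whole-cohort effect | Normalised weighting | Doubly robust | Restricted to patients outside V |
|---|---|---|---|---|
| 20% | −0.040 | −0.0554 | −0.0394 | −0.0394 |
| 20% | −0.032 | −0.0547 | −0.0388 | −0.0388 |
| 20% | −0.024 | −0.0556 | −0.0396 | −0.0396 |
| 40% | −0.040 | −0.0724 | −0.0399 | −0.0399 |
| 40% | −0.024 | −0.0718 | −0.0394 | −0.0394 |
| 40% | −0.008 | −0.0723 | −0.0401 | −0.0402 |

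Hand check at 40%: the treated mean comes from outside V, 0.10 + 0.05 − 0.04 = 0.11. The untreated mean is 0.15 + 0.4 × 0.08 = 0.182. The difference is −0.072, as simulated. Without normalisation the treated mean shrinks to 0.6 × 0.11 = 0.066, and the difference is −0.116.

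When V could also be treated, all whole-cohort estimators were within 0.0005 of the truth. With V untreatable, the weighted estimates were always off. The doubly robust estimate returned about −0.04 whatever the effect inside V: close when the effect was the same there, otherwise off by about 0.007 to 0.032. No treated patient in V exists to show which case applies. Restriction recovered the −0.04 of the treatable patients, which is a different target from the whole cohort.

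**The case against.** The strongest reply is that the sentence is loose wording in a condensed article. It at least names positivity, its list of methods is open-ended, and overlap weights and trimming belong to the propensity-weighting family. Details such as trimming limits are normal content for an analysis plan. That last part stands: a particular threshold is a matter of preference, and its absence is no fault here. The sentence itself is still a positive statement that is incorrect, and no later detail makes it true.

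Several stronger readings are tempting and should be resisted.

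- *That the planned treatment effects will be biased.* The bias in the illustration belongs to whole-cohort weights. The protocol states no target population for these analyses and does not say that they pool all centres and periods. Weights for the effect in the treated give the right answer when a drug was simply unavailable, though not where it was universal, since e/(1 − e) is then undefined.
- *That doubly robust estimates are biased too.* They are correct if the outcome-model extrapolation holds. The exact statement is that the whole-cohort effect rests on an assumption that the data cannot test.
- *That violations are certain in this study.* The documents describe many sites, several waves and differing clinical management. They do not say that any treatment was absent or universal anywhere.
- *That the main analysis is affected.* The sentence covers in-hospital interventions. The main exposure is the viral variant, and mortality is modelled with Cox and Fine and Gray models.

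**Conclusion.** The statement that these two methods account for positivity violations is wrong and should be corrected. The consequence is conditional. If some centre-periods had no treated or no untreated patients, and their mortality differed from the rest, whole-cohort inverse weighting would be biased. Under the assumed inputs the false risk ratio is 0.71 against a truth of 1.0, and between 0.71 and 1.25 over the range tried. The doubly robust whole-cohort effect would then depend on extrapolation, with errors of up to about 3 percentage points in the simulated scenarios. None of these sizes is a forecast for this study, since the protocol gives no mortality or treatment frequencies.

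One feature could hide the problem. The adjustment list, "Covariate adjustment will be used to control for potential confounding variables, including age, sex, ethnicity, co-morbidities" and so on, does not name calendar period. The list is open-ended, so this is not proof of omission. If period were left out of the propensity model, a lack of overlap between waves would not show in the estimated propensities and would act as confounding instead.

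The matter deserves correction because treatment response is a stated objective, but it does not touch the primary variant analysis.

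**What to change.** Remove the claim about positivity and state that inverse propensity weighting and doubly robust methods address measured confounding only. Then add:

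- For each treatment comparison, overlap will be checked by centre and calendar period.
- Each comparison will be restricted to centre-periods in which both options were in use. Alternatively, a weighting whose target population has overlap will be used: overlap weights or, where a treatment was only unavailable and never universal, weights for the effect in the treated.
- The number of patients excluded and the population to which the estimate applies will be reported with each result.

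Any trimming limit can be left to the analysis plan, with a note that trimming changes the target population.

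The cost is analysis-plan wording, a narrower target population and fewer patients per comparison. No change to data collection is needed if admission dates and centre are recorded, as the planned analyses by site, period and time from admission imply.
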